## Abstract

**Background:**

Active monitoring of hospitalised adults, using handheld electronic physiological surveillance systems, is associated with reduced in-patient mortality in the UK. Potential also exists to improve the recognition and response to deterioration in hospitalised children. However, the clinical effectiveness, the clinical utility, and the cost-effectiveness of this technology to reduce paediatric critical deterioration, have not been evaluated in an NHS environment.

**Method:**

This is a non-randomised stepped-wedge prospective mixed methods study. Participants will be in-patients under the age of 18 years, at a tertiary children’s hospital. Day-case, neonatal surgery and Paediatric Intensive Care Unit (PICU) patients will be excluded.

The intervention is the implementation of Careflow Vitals and Connect (System C) to document vital signs and sepsis screening. The underpinning age-specific Paediatric Early Warning Score (PEWS) risk model calculates PEWS and provides associated clinical decision support. Real-time data of deterioration risk are immediately visible to the entire clinical team to optimise situation awareness, the chronology of the escalation and response are captured with automated reporting of the organisational safety profile.

Baseline data will be collected prospectively for 1 year preceding the intervention. Following a 3 month implementation period, 1 year of post-intervention data will be collected.

The primary outcome is unplanned transfers to critical care (HDU and/or PICU). The secondary outcomes are critical deterioration events (CDE), the timeliness of critical care transfer, the critical care interventions required, critical care length of stay and outcome.

The clinical effectiveness will be measured by prevalence of CDE per 1000 hospital admissions and per 1000 non-PICU bed days.

Observation, field notes, e-surveys and focused interviews will be used to establish the clinical utility of the technology to healthcare professionals and the acceptability to in-patient families. The cost-effectiveness will be analysed using Health Related Group costs per day for the critical care and hospital stay for up to 90 days post CDE.

**Discussion:**

If the technology is effective at reducing CDE in hospitalised children it could be deployed widely, to reduce morbidity and mortality, and associated costs.

**Trial registration:**

Current Controlled Trials ISRCTN61279068, date of registration 03.06.19, retrospectively registered.

## Background

All-cause child mortality in the UK has not maintained improvement, in line with other European countries. The Confidential Enquiry into Maternal and Child Health deaths (CEMACH) ‘Why children die”, found that 25% of in-hospital deaths had identifiable failures in direct care and potentially avoidable factors in 43% [1, 2]. The factors included failure to recognise and respond effectively to deterioration. Paediatric Early Warning Scores (PEWS) and systems have been advocated as a mechanism to assist healthcare staff to identify deterioration so that care might be augmented to improve outcome. However, the evidence base underpinning their use in clinical practice is limited [1]. In the UK, despite reported use of PEWS by 85% of hospital treating children [3], there are more than 4000 emergency transfers to Paediatric Intensive Care Units per year from in-patient wards [4], suggesting that those patients deteriorated in hospital. The progression of deterioration to become critical, requiring admission to a high dependency unit (HDU) or the PICU is known to increase the length of hospital stay and the risk of mortality [5–7]. Evolving evidence suggests that PEWS may assist in reducing the severity of illness and the critical interventions required by patients who require unplanned emergency transfers to critical care [8, 9].

To date, PEWS research has been hampered by the use of paper-based charting of vital signs. Achieving implementation fidelity of PEWS systems have been challenging, with incomplete monitoring of the specific vital signs that contribute to PEWS reported. Additionally, there has been poor documentation of PEWS escalation, the timeliness of response and the associated clinical outcomes, which makes it difficult to assess if PEWS have been implemented as intended. In contrast, active monitoring of adult patients in hospital using an electronic physiological surveillance system has been in place for more than 10 years [10]. This technology has been associated with the standardisation of vital signs monitoring and has demonstrated a significant reduction in deaths at two large University hospitals in the UK [11]. That work contributed to the development of a National Early Warning Score (NEWS), a single risk model for identifying signs of early deterioration in adults [12–14].

### Why this study is necessary and the expected contribution to the field

The risk model developed for adults is unsuitable for use in children for a number of reasons;
age-associated variation in physiological signs including heart rate, respiratory rate and blood pressure, from birth to adulthood, mean that a single PEWS risk model would be inadequate to flag deterioration across the age ranges [15–18].the ability to physiologically compensate for serious illness is limited in children, providing a shorter window of opportunity for staff or parents to recognise the signs and to respond quickly, to avoid the progression of deterioration to become critical [19, 20].

To date, there is no technology similar to that used in adults, which has been robustly tested for use for children in hospital, for screening physiological signs using an underpinning age-specific PEWS risk model. The most extensive randomised study of PEWS in an international context, the EPOCH study, did not demonstrate a reduction in mortality associated with the use of PEWS [1]. A lower observed event rate for mortality occurred in both arms, of the intervention and comparison sites. The observed mortality was lower than the data used for the computation of the sample size estimate (2007 data from fourteen hospitals). The study also highlighted the challenge in achieving complete data capture of the required vital signs which contribute to PEWS when paper-based documentation was used. Less than 5% of all the recorded data reviewed [1] were complete for recording of the seven components which had contributed to the validation of the bedside PEWS.

The development of electronic physiological surveillance systems suitable for use in a paediatric population is complex and expensive, potentially deterring industry from developing age-specific products. To address this deficit, The Learning Clinic (now System C) collaborated with this research team to develop technology underpinned by scientific evidence. Proof-of-concept testing of the VitalPAC Paediatric prototype occurred at this hospital site, alongside existing practice. When compared to paper charts, VitalPAC Paediatric demonstrated improved the accuracy of vital sign documentation; 98.5% Vs 85.6% *p* < 0.02; PEWS calculation; 94.6% Vs 55.7% *p* < 0.02 and reduced the documentation time; 68 Vs 98 s *p* < 0.002 [21].

Sepsis is a major cause of deterioration, therefore addition of a paediatric sepsis [22, 23] clinical prompt, including laboratory and clinical data was tested. This demonstrated 71% sensitivity and 81% specificity when two or more components were present, suggesting it could be an effective tool to prompt nurses and doctors to consider sepsis earlier. The staff using the technology perceived that this mode of documentation improved safety and increased team situation awareness.

This study is the whole hospital evaluation of electronic physiological surveillance technology to provide pro-active monitoring for paediatric in-patients.

## Methods/design

SMART technology, self-monitoring and reporting technologies, such as electronic physiological surveillance systems have the potential to provide an end-to-end solution for recognising and responding to serious illness or deterioration in children. The study aims to:
Standardise the process for monitoring vital signs for children in hospitalImprove the detection of early signs of clinical deterioration, including sepsisProvide real-time data to the entire clinical team to improve team situation awareness about deteriorating patientsUse clinical decision support to prompt the pro-active management of deterioration, and early stabilisation of patient, reducing the progression of deterioration to become criticalReduce emergency transfers to critical care following deterioration in hospitalTo prompt timely transfer of deteriorating patients to critical care, who were non-responders to first-line stabilisation interventions

### Study design

This is a non-randomised stepped-wedge prospective mixed methods study exploring the clinical effectiveness, clinical utility and cost-effectiveness of an electronic physiological surveillance system to provide active monitoring of paediatric patients and to screen for early signs of serious illness, deterioration or sepsis.

#### Population and setting

The participants will be ward in-patients, aged less than 18 years, at a tertiary children’s hospital in the United Kingdom. The study site has 240 in-patient beds, a large emergency department, a 24-bed PICU, a 19-bed HDU and a 4-bed long-term ventilation Unit (LTVU).

The patient profile will include a mix of general paediatric medical and surgical patients and tertiary specialties including oncology, cardiology/cardiac surgery, neurology/neurosurgery, burns, respiratory, renal and orthopaedics. Day-case patients, patients in the neonatal surgical unit or in the PICU will be excluded.

The hospital does not have a Medical Emergency Team or a Critical Care Outreach Team. Patient deterioration is managed by the core clinical team. During the out-of-hours period, patients are managed by the on-call team. If a call to the resuscitation team is made, the responding team comprise of a senior nurse, senior paediatric registrars, resuscitation training officers (day-time only Monday to Friday), the Paediatric Intensive Care registrar and/or an anaesthetist.

#### The intervention

The intervention is an electronic physiological surveillance system suitable for use in children in hospital. This is composed of health IT software Careflow Vitals (previously known as VitalPAC) configured with an underpinning age-specific PEWS risk model, which runs wirelessly on Apple hand-held devices. The technology is used to manually document vital signs to screen for early signs of serious illness or deterioration, including sepsis. The software prompts an active monitoring process by standardising the complete documentation of vital signs and clinical assessments, at a frequency linked to the child’s PEWS. The completed PEWS are categorised as low, moderate, high or critical risk for deterioration, with associated decision support prompted for each. When a suspicion of sepsis has been documented, a complete sepsis assessment is required to stratify the clinical concern regarding sepsis using the NICE sepsis pathway [22], this prompts targeted care delivery and captures the time critical sepsis bundle compliance.

Careflow Vitals is used in conjunction with Careflow Connect; a secure encrypted communication system for professionals to provide real-time data to the entire clinical team on hand-held devices. Automated alerts about high or critical PEWS categorisation are sent to the Nurse in Charge of the ward and to the responsible clinical team. The chronology of escalation, response and associated actions are captured.

There will be phased implementation of the technology ward by ward, with concurrent assessment of the implementation fidelity. Weekly organisational safety reports will be fed back to wards, clinical teams and managers. These will collate reporting of the completeness and frequency of assessment, active management of patients with high or critical PEWS or new sepsis concerns, and the timeliness of emergency transfers to critical care.

### Comparison

Baseline data will be collected prospectively for 1 year preceding the intervention, with patient monitoring of vital signs and sepsis screening recorded in the Electronic Patient Record (Meditech 6). The hospital standard for the monitoring of vital signs for children in hospital, is set out in a clinical policy, together with the expected escalation and response processes. All of the component parts required for the calculation of a core PEWS (respiratory rate, effort of breathing, oxygen saturation (SpO2), oxygen delivery (FiO2), heart rate, capillary refill time and nurse concern) are mandated within the EPR each time vital signs are recorded. Temperature is also recorded but it does not contribute to the PEWS. For new admissions, PEWS score 3 or more or clinical concern, requires that an extended PEWS is undertaken. This incorporates additional vital signs alongside the core PEWS; which include blood pressure, AVPU (rapid neurological assessment of responsiveness; Alert-Verbal-Pain-Unresponsive) and parental concern. The process for communication for concern of deterioration is through the traditional bleep process.

Following a 3 month implementation period, 1 year of post-intervention data will be collected.

#### Outcomes

The primary outcome is unplanned transfers to critical care, either to HDU and/or PICU.

The secondary outcomes are critical deterioration events [24], the patients who had unplanned transfers from in-patient wards to critical care (HDU and/or PICU) and required organ support in the following 12 h. The CDE prevalence per 1000 hospital admissions and per 1000 non-ICU bed days will be reported. The timeliness of critical care transfer will be reported using the Children’s Resuscitation Intensity Scale (CRIS) [25]. The severity of illness at unplanned transfer to PICU; the Prognostic index of Mortality (PIM3 [26], the requirement for critical care interventions (mechanical ventilation, non-invasive ventilation, inotropes and/or dialysis), length of critical care stay and outcome. We will report the sepsis screening, suspicion of sepsis, clinical confirmation of ‘treat as sepsis’, the NICE sepsis bundle compliance and associated outcome.

The activation of the resuscitation team for cardiac arrests, respiratory arrests, or peri-arrest situations in the in-patient wards (excluding PICU) will be reported. All-cause mortality will be reported for the wards included in the study. The overall critical care activity; total admissions, bed days, length of stay, refused admissions (internal/external) and cancellations of planned major surgery due to lack of critical care capacity, will be reported.

#### Sample size

The study will collect data from 240 in-patient beds. Based on existing hospital data, over 12 months 300–350 emergency transfers to HDU and/or PICU from in-patient wards would be expected. Previously published work from this centre [8] suggested that a robustly implemented process for proactively recognising and responding to deterioration in hospital, would contribute to a 30% reduction in total bed days following a CDE, with a median reduction of two critical care bed days per CDE. This is projected to be sufficient for the analysis planned.

The projected 80–100% bed occupancy in 240 beds is expected to yield a minimum of 6 sets of vital signs/per bed/per day, which is expected to yield a minimum of 630 K–780 K observation sets per year.

#### Data analysis

The data analysis is broken down into the four main work-packages in the study.
The quantitative analysis of the clinical effectiveness at reducing critical deterioration, will report the prevalence of CDEs per 1000 hospital admissions and per 1000 non PICU bed days to compare the baseline and intervention arm of the study.The predictive ability of the age-specific PEWS risk model, will be reported using the sensitivity, specificity, positive/negative predictive values Modelling of the physiological values will be used to determine evidence-based thresholds for vital signs and logistic regression models will be developed to determine the weighting of components of the PEWS risk model to improve the performance at improving early detection of signs of deterioration. The study will use statistical process control techniques and will explore the feasibility of using stochastic control methods to track the condition of patients over-time to develop a longitudinal component (trend changes in vital signs), within the risk model.The qualitative analysis will focus on the clinical utility of the technology to assist in the recognition and response to deterioration in children in hospital. It will also aim to evaluate the acceptability to children and their families of being monitored in this way. The three core methods which will be used are ethnographically driven observation and conversational interviews, short e-surveys, and focused interviews. Qualitative analysis will use an interpretive, reflexive, conceptual thematic analytical approach [27, 28] the integration of descriptive codes and themes into robust concepts via Morse’s four cognitive analytical processes [29].The analysis of proactive sepsis screening for all patients will describe the prevalence of pre-existing risk factors for sepsis, the cases where sepsis was suspected, the subset where the clinician made a decision to treat as sepsis (blood cultures and intravenous antibiotics), NICE sepsis bundle compliance and associated outcome. Multi-variate modelling will be also be used to determine the components of the sepsis assessment which would contribute to improved discrimination of evolving sepsis.The cost-effectiveness of the technology will be analysed using Health Related Group (HRG) costs per day for the critical care and hospital stay following a CDE for up to 90 days, pre and post intervention. The societal perspective will be used and the time horizon is 1 year. For medical direct costs, patient level hospital costs will be computed by using hospital costs and published tariffs where appropriate. Indirect costs include work absenteeism in the parents of children who had an in-hospital deterioration, and productivity losses resulting from the sequelae of critical illness.

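### The declared primary outcome is unplanned transfers to HDU/PICU, but effectiveness is measured and compared on CDE, a secondary subset of those transfers

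*Protocol article*

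**What the plan says.** The Outcomes section is unambiguous: "The primary outcome is unplanned transfers to critical care, either to HDU and/or PICU". The abstract's Method paragraph names the same primary outcome. Both places list CDE as secondary. Outcomes defines a CDE as an unplanned ward-to-critical-care transfer in a patient who was moved "and required organ support in the following 12 h", so every CDE is also a primary-outcome event.

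The statements about how effectiveness is judged use CDE instead:

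- Abstract, Method: "The clinical effectiveness will be measured by prevalence of CDE per 1000 hospital admissions and per 1000 non-PICU bed days".
- Data analysis, clinical effectiveness item: the analysis "will report the prevalence of CDEs per 1000 hospital admissions and per 1000 non PICU bed days to compare the baseline and intervention arm".
- Abstract, Discussion: "If the technology is effective at reducing CDE in hospitalised children it could be deployed widely". The main Discussion closes on the same condition.

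Sample size gives an expected 300–350 emergency transfers in 12 months. Its effect size is a third quantity: a 30% fall in total bed days after a CDE, with a median saving of two critical care bed days per CDE.

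**The concern.** The primary outcome is the one on which a study's main claim should stand or fall. Here the article gives that status to transfers and then states, in two places, that a different outcome measures effectiveness. The result for transfers is left with no stated role in the effectiveness judgement: if transfers were unchanged or rose, nothing in the stated effectiveness measure would register it.

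The design is non-randomised and before-after in its main comparison, and registration was retrospective. In that setting, readers rely heavily on a clear prior statement of which result decides the question.

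**Working it through.** **1. Textual check.** Each place that assigns a role to an endpoint, side by side:

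| Place | Role | Endpoint |
|---|---|---|
| Abstract, Method; Outcomes | primary outcome | unplanned transfers |
| Abstract, Method; Outcomes | secondary outcome | CDE |
| Methods/design, aims | aim | fewer emergency transfers |
| Abstract, Method | measure of clinical effectiveness | CDE rate, two denominators |
| Data analysis | baseline v. intervention comparison | CDE rate, two denominators |
| Abstract, Discussion; Discussion | condition for deployment | CDE |
| Sample size | expected count | transfers |
| Sample size | effect size | bed days after a CDE |

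No item under Data analysis mentions a comparison of transfers, and the article gives them no rate or denominator.

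**2. Does the choice of endpoint matter numerically?** The article states no alpha, power or target rate reduction, so there is no figure of its own to reproduce. What follows is an illustration.

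Inputs: baseline transfers E = 300–350 (Sample size); equal exposure in the two years (one year each); two-sided 5%, 80% power and Poisson variance (assumptions); CDE share of transfers 33–50% (assumption), giving about 0.33 × 300 ≈ 100 to 0.50 × 350 = 175 CDEs a year.

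The detectable rate ratio RR solves −ln(RR) / √(1/E + 1/(E·RR)) = 1.96 + 0.84 = 2.80.

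| Endpoint | E | Detectable RR |
|---|---|---|
| Transfers | 300 | 0.783 |
| Transfers | 350 | 0.799 |
| CDE (assumed share) | 100 | 0.638 |
| CDE (assumed share) | 175 | 0.721 |

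Check at E = 100: −ln(0.638) = 0.449; √(0.0100 + 0.0157) = 0.160; the ratio is 2.80.

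Overdispersion worsens all four. With the variance doubled, the detectable reduction in transfers goes from 20–22% to 28–30%.

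**3. Can the two endpoints give different answers?** Power is Φ(|ln RR| / √(1/E + 1/(E·RR)) − 1.96). Take E = 300 transfers, half of them CDEs (assumption).

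- CDEs fall by 30% and other transfers do not change: CDEs go from 150 to 105 and transfers from 300 to 150 + 105 = 255, a 15% fall. Power is 80% on CDE and 48% on transfers.
- Both fall by 20%: power is 45% on CDE and 73% on transfers.

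Either endpoint can be the more sensitive, depending on where the effect falls. The two are therefore not substitutes, even though one is contained in the other.

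**The case against.** The strongest reply is that this is a condensed article. Transfers are the declared primary outcome of a design with one baseline year and one post-intervention year, and reducing them is a stated aim, so a before-after comparison of transfers is the natural reading. The denominator and model may properly sit in a full protocol or SAP. The Data analysis sentence is also scoped to reducing critical deterioration, which is what CDE captures. The Discussion gives a reason for the emphasis: admission thresholds vary, so separating out CDEs is useful.

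Much of this stands, and it rules out several stronger readings that a reader might infer:

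- **That transfers will not be compared at all.** The article states no such comparison, but it does not say there will be none, and the full protocol and SAP are not shown.
- **That an outcome switch is built in, or that CDE is the wrong endpoint.** Both outcomes are pre-specified and openly ranked. The deployment sentences are conditional remarks, not decision rules. Nothing in the article shows which endpoint ought to be primary.
- **That there are several separate chances to claim success.** The stated effectiveness comparison is CDE alone. Its two rates share a numerator and are strongly related.
- **That transfers will rise while CDE falls.** The aim to "prompt timely transfer of deteriorating patients to critical care" concerns when non-responders are moved. It does not say that more children should be. Divergence is possible but not predicted.

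What does not stand is the appeal to an unseen document. The article is not silent on the effectiveness measure: it fixes it as CDE in the abstract and carries only CDE into the comparison. The abstract lacks even the narrower scope of the Data analysis sentence. An SAP that made transfers decisive would contradict these statements. One that followed them would leave the declared primary outcome outside the effectiveness judgement.

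**Conclusion.** The point holds as an internal contradiction. The declared primary outcome and the stated measure of effectiveness are different endpoints, the second a secondary subset of the first, and the sample size section rests on a third quantity. This should be put right before analysis, because it settles which result supports the study's conclusion.

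Confidence is high for the textual mismatch, which needs no arithmetic. The size is illustrative: a detectable rate ratio of about 0.78–0.80 on transfers against about 0.64–0.72 on CDE. It depends on the assumed 33–50% CDE share, Poisson variance, equal exposure, two-sided 5% and 80% power.

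**What to change.** Let one endpoint, on one named denominator, decide effectiveness, and say so consistently.

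- **Most direct route:** keep unplanned transfers primary. State in the abstract's Method paragraph and in Data analysis that their rate is compared between the baseline and post-intervention years. Make the CDE rate the key secondary outcome, analysed in the same way.
- **Alternative:** declare CDE primary, as a dated change with reasons.

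Under either route, bring Sample size (at present bed days after a CDE) and both deployment statements into line with the choice. State that any divergence between transfers and CDE will be reported openly.

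No new data are needed for the comparison, since transfers must already be identified in order to derive CDEs. The cost is wording, plus restating the sample size basis for the chosen endpoint. The downside of the direct route is that a fall in CDE alone would no longer support the headline claim. The downside of the alternative is that the deciding endpoint rests on fewer events, and a late change of primary outcome has to be justified openly.

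### Hospital costs are counted only after a CDE, an event the technology is meant to reduce, so the before-after cost comparison can mislead and leaves out non-CDE transfers

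*Protocol article*

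**What the plan says.** The cost-effectiveness work-package in the Data analysis section uses HRG "costs per day for the critical care and hospital stay following a CDE for up to 90 days, pre and post intervention". The abstract gives the same frame. The work-package continues: "The societal perspective will be used and the time horizon is 1 year". For direct medical costs, "patient level hospital costs will be computed by using hospital costs and published tariffs where appropriate"; that sentence names no patient group of its own. On the indirect side: "Indirect costs include work absenteeism in the parents of children who had an in-hospital deterioration, and productivity losses resulting from the sequelae of critical illness".

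The Outcomes section defines CDEs as the subset of patients who had "unplanned transfers from in-patient wards to critical care (HDU and/or PICU) and required organ support in the following 12 h". The primary outcome is wider: every unplanned transfer to HDU and/or PICU, with or without organ support. The Sample size section expects 300–350 emergency transfers over 12 months, gives no number of CDEs, and states the expected benefit as a 30% fall in total bed days after a CDE together with "a median reduction of two critical care bed days per CDE".

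**The concern.** The costed set is defined by something that happens after the intervention starts and that the intervention is designed to change. The study aims both to reduce emergency transfers and to prompt timely transfer of children who do not respond to first-line stabilisation, so the children who still have a CDE afterwards need not resemble those who had one at baseline. Two distinct problems follow.

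- **Per-CDE summary.** A mean cost per CDE mixes a change in cost with a change in who is counted. Removing inexpensive cases raises the mean even though money is saved.
- **Total post-CDE cost.** A sum captures avoided CDEs, but transfers without organ support are not in the stated cost set. If a child who would have had a CDE is transferred earlier and needs no organ support, the whole stay leaves the account although it still has to be paid for.

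The article's Discussion in the abstract links wide deployment to lower associated costs, so the direction and size of the cost result matter. There is also a smaller matter of frame: hospital stay is costed for 90 days within a 1-year horizon, and parental absenteeism is counted for children with an in-hospital deterioration, a group not defined as those with a CDE.

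**Working it through.** The article gives no CDE count, severity mix, distribution of stay or cost per day, so there is no economic figure to reproduce. The numbers below are assumptions that show the mechanism. Cost is taken as proportional to critical care days (one constant cost per day).

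Formulas, with m mild CDEs at a days each and s severe CDEs at b days each: total = m·a + s·b; mean = total / (m + s).

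**1. Per-CDE summary, first assumed mix (a = 3, b = 12)**
- Baseline, m = 70, s = 30: total = 210 + 360 = 570; mean = 570/100 = 5.7.
- 28 mild CDEs prevented, m = 42, s = 30: total = 126 + 360 = 486; mean = 486/72 = 6.75.
- Change: mean 6.75/5.7 − 1 = +18%; total 486/570 − 1 = −15%.

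**2. Does the reversal depend on the mix? Second assumed mix (m = s = 50, a = 4, b = 12; total 800, mean 8.0)**

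| After the intervention | Total days | Mean per CDE | Change in total | Change in mean |
|---|---|---|---|---|
| 25 mild prevented | 700 | 9.33 | −12.5% | +16.7% |
| 30% prevented evenly | 560 | 8.0 | −30% | 0 |
| 25 severe prevented | 500 | 6.67 | −37.5% | −16.7% |

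With 25 of 50 mild CDEs prevented, and mild stays of 2–6 days and severe stays of 8–20 days, the mean rises by 4.8% to 27.3% and the total falls by 4.5% to 21.4%. The sign reverses when milder cases are the ones prevented. With even prevention the mean shows no benefit at all, and with severe cases prevented both measures fall.

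**3. Summed post-CDE cost, second mix**
- Suppose 25 mild CDEs become non-CDE transfers of 3 days each. Post-CDE days go from 800 to 700, an apparent saving of 100. Adding the 25 × 3 = 75 uncounted days gives 775, so the real saving is 25.
- Suppose there are also 50 new non-CDE transfers of 2 days, adding 100 days. The account still shows 700, but the days over these transfers are 700 + 75 + 100 = 875, an increase of 75 on 800.
- Non-CDE transfers already present at baseline are taken as unchanged and left out of both sides. Including them would not alter the differences in days.

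**4. Time frame.** 90/365 = 24.7% of the stated horizon.

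**The case against.** The strongest reply is that the Data analysis section fixes no per-CDE mean. It compares costs before and after, each period is one year, and the Sample size section also speaks of total bed days. A sum per period would count avoided CDEs correctly. That stands, and it limits the sign reversal to a per-CDE summary. It does not answer the third step of the working, because a sum over CDEs still omits the other transfers.

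Several stronger readings are tempting, and the article does not support them:

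- *Stays are compared only after a CDE.* They are not. The Outcomes section also reports overall critical care admissions, bed days and length of stay, so extra activity would be visible. It is not said to be costed.
- *A lower transfer threshold by itself dilutes the per-CDE mean.* A CDE needs organ support within 12 h. Children transferred more readily without it never enter that mean; their effect is omitted cost.
- *90 days contradicts 1 year.* A shorter window for hospital stay can sit inside a longer horizon that also covers "productivity losses resulting from the sequelae of critical illness". The relation is unexplained, not impossible.
- *Technology costs are excluded.* The article does not name software, device or training costs, but it condenses a fuller protocol that is not shown. This is only something to confirm there.

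It is also fair that every stay and mix used above is assumed.

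**Conclusion.** The concern holds in a limited form. The stated hospital cost set is conditioned on an event the technology is meant to reduce, and it is narrower than the primary outcome. A per-CDE summary can then point the wrong way (+18% against −15% in one assumed mix; +4.8% to +27.3% against −4.5% to −21.4% over a range), but only where milder CDEs are the ones prevented. A summed comparison avoids this, yet can overstate a saving or show one where transfer days rise (700 counted against 875 actual, from 800, in the assumed example). The directions follow from the definitions; the sizes rest on the assumed stays and on a constant cost per day. The mismatch between the indirect-cost population and the CDE set, and the unexplained relation of 90 days to 1 year, are secondary points of clarity. The primary outcome is unaffected. This is a worthwhile improvement to the economic work-package.

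**What to change.** Make the main economic comparison the total critical care and hospital cost of all unplanned transfers, CDE and non-CDE, per 1000 eligible admissions in the baseline and post-intervention years, and report the incremental cost per CDE avoided. Keep cost and stay per CDE as descriptive results, including "length of critical care stay and outcome" when given for CDE patients alone. State one patient population for direct and indirect costs. Add a sentence saying how the 90-day hospital window fits the 1-year horizon, or use a single horizon for all costs. Confirm in the full protocol that the cost of the technology is counted.

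The cost is modest. Transfers are already counted for the primary outcome, admissions already serve as a denominator for the CDE rate, and HRG day costs are already planned. The added work is to cost the non-CDE transfers, which are some part of the expected 300–350 a year (at that rate 600–700 transfers of all kinds over the two years). One limit remains: a child stabilised on the ward without transfer contributes nothing to this total, so the hospital-stay part may overstate savings. Showing the critical care part separately deals with this without costing every admission.
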